#### Secondary outcome measures

Secondary outcomes include Quality of Life measured by the EuroQol-5D-5L (EQ-5D-5L), Activities of Daily Living (ADL), Pittsburgh Sleep Quality Index (PSQI) [29], intrinsic capacity, frailty, social support, and intervention cost and benefit, which have been validated among Chinese older adults. Intrinsic capacity will be evaluated in accordance with the WHO Integrated Care for Older People (ICOPE) guidelines [30], across the following domains: cognitive capacity assessed by MoCA-B, vitality assessed using Mini Nutritional Assessment–Short Form (MNA-SF), locomotion measured by Short Physical Performance Battery (SPPB), psychological status assessed using Patient Health Questionnaire (PHQ-9) [31], and sensory determined by self-reported vision and hearing questions. Frailty will be assessed using the frailty phenotype (FP) [32, 33], physical activity levels will be evaluated using the International Physical Activity Questionnaire–Short Form (IPAQ-SF), and social support will be assessed by the Lubben Social Network Scale (LSNS) [34].

Secondary outcomes will be assessed at baseline, 6 weeks, 12 weeks, and 24 weeks post-randomization. Secondary endpoints will be defined as the between-group differences in change from baseline at each post-randomization timepoint. Results will be reported as adjusted mean differences or risk differences with corresponding 95% confidence intervals, as appropriate to the outcome type. All secondary analyses will follow the intention-to-treat principle.

#### Process evaluation

A comprehensive process evaluation will be conducted to assess the quality of intervention implementation and its potential impact on study outcomes. This evaluation will address the following dimensions: Eligibility and recruitment will be tracked using data on the proportion of eligible participants, recruitment and retention rates, and reasons for drop-off. Intervention acceptability will be evaluated through supervisory documents, adherence records and satisfaction surveys [35]. Adherence will be measured based on the number of dropouts and session frequency across groups. Participants will be classified as having dropped out if they meet any of the following criteria: average training frequency of ≤ 2 times per week over 3 weeks; average frequency of ≤ 1 time per week for two consecutive weeks; or no sessions completed within a 1-week period. Temporary absences of 1–2 weeks due to medical treatment or personal reasons will be exempt if participants resume full participation thereafter. All dropouts will be encouraged to complete follow-up assessments.

Outcome acceptability will be assessed by calculating the completion rates of outcome questionnaires at baseline, 6 weeks, and 12 weeks. Adverse events, including falls, fractures, muscle strains, cardiovascular events, and new or exacerbated musculoskeletal, cardiovascular, or metabolic conditions, will be monitored throughout the study. Participants in the intervention group will be asked about any adverse events following each session. All reported events will be documented and the responsible authorities will be notified promptly, and relevant free examinations and management strategies will be provided within the nursing home or referred to the appropriate medical institution. Participants experiencing minor adverse events may continue with the study if the participants’ condition does not worsen and if adequate rest and treatment do not interfere with ongoing participation.

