### Intervention

#### Intervention group

Participants in the intervention group will receive a 12-week, group-based multicomponent exercise program to be delivered through in-person, face-to-face sessions. Each session will last 30 min and will be conducted twice per week. The multicomponent exercise intervention will consist of five structured components: a warm-up, aerobic training, resistance training, mind–body training, and a cool-down period, forming a complex, theory-informed approach tailored to the physical and cognitive needs of older adults. Participants will be guided by nurses in the nursing home to perform aerobic training, resistance training, and dual-task (mind–body) training throughout the 30-min session. A Rate of Perceived Exertion (RPE) of 5–6, corresponding to moderate intensity, will be recommended. Core aerobic exercises will include shoulder movements, hip abduction or extension, and thigh lifts. Resistance training will consist of functional movements such as squats and trunk twists. Mind–body training will incorporate coordinated activities such as seated marching combined with attention tasks and standing marching paired with inhibition tasks. All participants will be instructed to complete a brief warm-up at the beginning and a cool-down routine at the end of each session to promote safety and recovery.

The intervention will feature a group-based multicomponent exercise program and will be conceptually grounded in the integrated HAPA-TPB model. This theoretical framework was selected to address known facilitators and barriers to exercise engagement among older adults [23], as it incorporates both the motivational phase (e.g., intention formation) and the intenders phase (e.g., planning, execution, maintenance of behavior) and action phase, thereby providing a comprehensive framework for promoting sustainable health behavior change in later life. This integrated model combines the stage-based behavioral pathway of HAPA (preintenders, intenders, and actors) [24, 25] with key motivational determinants from TPB, including attitudes, subjective norms (operationalized as social support in this study), and perceived behavioral control [26]. Particular emphasis was placed on enhancing self-efficacy and peer-based social support as core mechanisms to strengthen adherence and sustain exercise behavior.

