#### Control group

Participants in all study groups, including the control group, will receive routine nursing home care unrelated to structured exercise or cognitive training. Usual care will encompass three main components: (1) *basic care*, maintaining a clean, well-ventilated, and tidy living environment; assistance with personal hygiene (e.g., bathing and clothing changes twice per week); and toileting support for individuals with incontinence or limited mobility; (2) *nutritional care*, provision of three meals per day according to the nursing home’s standard schedule, with feeding assistance provided as needed; and (3) *safety care*, participants remain in designated indoor areas, and assistive devices are provided when necessary to ensure safe mobility.

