### Measurements

#### Primary outcome measures

All outcome data will be collected through a face-to-face electronic questionnaire system administered by trained physicians or nurses who have received standardized training. The primary outcome is cognitive function measured by the Montreal Cognitive Assessment-Basic (MoCA-B) score. The MoCA-B is a validated screening tool specifically developed to detect mild cognitive impairment (MCI) in individuals with limited educational backgrounds or illiteracy [27, 28]. It evaluates a range of cognitive domains, including executive function, immediate and delayed recall, verbal fluency, orientation, calculation, abstraction, visuoperception, and naming. The assessment takes approximately 15 min to complete and is scored out of a maximum of 30 points. To reduce potential bias related to education and literacy, one point will be added to the total score for participants with fewer than 4 years of education or those identified as illiterate (defined as the inability to read or write fluently in daily life), provided their raw score is below 30.

MoCA-B will be assessed at baseline, 6 weeks, 12 weeks, and 24 weeks post-randomization. The primary endpoint is defined as the between-group difference in change from baseline to 12 weeks post-randomization (end of the intervention period). Results will be presented as adjusted mean differences with 95% confidence intervals. All primary analyses will follow the intention-to-treat principle.

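### Dropouts are to be counted across groups by a training-session rule that has no meaning for controls and, read literally, catches full attenders; questionnaire completion is tallied only to week 12

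*Protocol article*

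**What the plan says.** Under Process evaluation, the protocol article says: "Adherence will be measured based on the number of dropouts and session frequency across groups". A participant is then classed as a dropout on meeting any one of three criteria:

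- "average training frequency of ≤ 2 times per week over 3 weeks"
- "average frequency of ≤ 1 time per week for two consecutive weeks"
- "no sessions completed within a 1-week period"

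Absences of one to two weeks for medical or personal reasons are exempt if the participant then resumes in full. Dropouts are to be encouraged to attend the remaining assessments.

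On the exercise schedule, the Intervention group section says: "Each session will last 30 min and will be conducted twice per week". The programme lasts 12 weeks. The Control group section says that participants "will receive routine nursing home care unrelated to structured exercise or cognitive training", and the Study design section confirms that controls get no structured exercise.

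Outcome acceptability is to be judged by the "completion rates of outcome questionnaires at baseline, 6 weeks, and 12 weeks". The Primary outcome measures section says: "MoCA-B will be assessed at baseline, 6 weeks, 12 weeks, and 24 weeks post-randomization". Secondary outcomes follow the same four time points. The analysis section puts week 24 into the mixed model and explores long-term (baseline to week 24) and durability (week 12 to week 24) effects.

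Three other items bear on retention. Process evaluation also tracks retention rates and the reasons for leaving. The section on trial flow and baseline characteristics plans a CONSORT diagram, and it also plans a comparison of those who complete follow-up with those lost to it.

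**The concern.** A count that is meant to be set side by side for two arms must be defined in both. This one is defined by an activity that only one arm is offered. The resulting control figure would be fixed by how the rule is read and would carry no information about who left.

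The rule also appears to conflict with the programme it monitors, because its first threshold equals the full scheduled frequency.

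The one process measure that works identically in both arms, questionnaire completion, is given an explicit list of visits that leaves out the last one.

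What is at stake is the feasibility report. The abstract lists intervention feasibility among the secondary outcomes, and the Introduction makes it an aim of the trial. The plausibility of the missing-at-random assumption is also judged by looking at missing outcomes in each arm, which a count of missed sessions does not show.

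**Working it through.** The article gives no numerical result for this measure, so there is no stated figure to reproduce. The check applies the rule as written to each arm's schedule.

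**Inputs**

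- Randomized: 78 per arm (Abstract, Results).
- Scheduled sessions, intervention arm: 2 per week in weeks 1 to 12, none afterwards (Intervention group).
- Scheduled sessions, control arm: 0 per week (Study design; Control group).
- Dropout if any one criterion is met: mean of 2 or fewer per week over 3 weeks; mean of 1 or fewer per week for 2 consecutive weeks; none in 1 week (Process evaluation).

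**Control arm**

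The mean is 0 per week. Criterion 1: 0 ≤ 2, met. Criterion 2: 0 ≤ 1, met. Criterion 3: no sessions in a week, met. The exemption for temporary absence does not help, since a control has no sessions to resume. The literal count is 78 of 78. If the rule is taken not to apply, the count is 0 of 78. In both cases the figure is the same whether no controls leave or many do.

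**Intervention arm, perfect attendance**

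Sessions over 3 weeks: 2 × 3 = 6. Mean: 6 / 3 = 2.0 per week. Criterion 1: 2.0 ≤ 2, met. The absence exemption is irrelevant because nobody was absent. No schedule above two sessions per week is described, so 2.0 is the highest mean available and every participant meets criterion 1. Criteria 2 and 3 then add nothing.

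**Weeks 13 to 24**

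No sessions are scheduled in either arm, so the rule has nothing valid to count in that period.

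**Completion rate**

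| | Baseline | Week 6 | Week 12 | Week 24 |
|---|---|---|---|---|
| Outcomes assessed | yes | yes | yes | yes |
| Completion rate calculated | yes | yes | yes | no |

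Three of the four assessment times are covered, or two of the three after baseline. The omitted visit is the one on which both the long-term and the durability contrasts depend.

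**Sample size**

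The stated sample size is not affected. With effect size 0.54, two-sided alpha 0.05 and 85% power, the two-sample t-test needs 62.56, rounded up to 63 per arm, or 126 in total as stated. Allowing for 20% attrition gives 126 / 0.80 = 157.5, or 158, close to the stated target of 160.

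**The case against.** The strongest reply is that these measures were never offered as measures of retention. The sentence on dropouts is about adherence, and the completion rate is about acceptability. A training-frequency rule is naturally applied only to people assigned to training, and nobody would publish 78 control dropouts. On this view the reference to both groups is loose wording. The text also separates the two ideas to a degree: dropouts may still be assessed, and the trial-flow section uses a different term, lost to follow-up. A condensed article may leave the operational definition of that term to the full protocol or SAP.

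Much of this stands. A reader might infer three stronger things, none of which the document supports:

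- *That retention by arm cannot be shown at all.* Retention rates, the CONSORT diagram and the lost-to-follow-up comparison can show it, including at week 24.
- *That the primary result is biased.* The primary endpoint is at week 12, which the completion rate covers. The analysis is by intention to treat, dropouts are still encouraged to attend assessments, and the model uses all available visits. The article also does not tie its per-protocol set to the dropout rule, so it cannot be said that the rule empties that set.
- *That the completion rate will overstate final follow-up by a known amount.* The 20% attrition allowance is not tied to week 24. It serves a sample size for an endpoint at week 12, so it does not size the gap.

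The objection does not remove the defect in what is written. The article does state a scope (both groups), a rule (session counts) and a list of visits (to week 12). The scope does not fit the rule, the rule does not fit the twice-weekly schedule, and the list does not fit the assessment schedule. These are statements that conflict, not details left for another document.

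**Conclusion.** The point holds as a limited one about the process evaluation. As written, the dropout count has no meaning in the control arm (78 or 0 of 78, depending only on the reading) and cannot compare the arms. In the intervention arm the first criterion, taken literally, labels full attenders as dropouts, so the Intervention group and Process evaluation sections must be reconciled; which of them should change is for the investigators. The completion rate omits one of three post-baseline visits.

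No estimate, test or sample size changes. The consequence is an uninformative or misleading adherence figure for an outcome that the abstract lists, and an acceptability figure that does not reach the visit used for the exploratory long-term and durability contrasts. The conclusion rests on the criteria being applied as worded and on no exercise sessions being scheduled for controls or after week 12, as the article states.

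**What to change.** - Report session-based adherence and discontinuation of exercise for the intervention arm only, and reconcile the first dropout criterion with the twice-weekly schedule.
- Compare the arms on loss to follow-up, defined identically in both as no MoCA-B at the visit, with the reason recorded, at weeks 6, 12 and 24. Use the same definition in the CONSORT diagram and in the comparison of completers with those lost to follow-up.
- Extend the questionnaire-completion rate to week 24 and give it by arm.

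The cost is mainly wording. The assessments are already scheduled at each of these visits, and reasons for leaving are already to be tracked. The downside is that the reported completion may look less favourable once the last visit is included.

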	Enhance outcome expectations	During the introductory session (week 0), participants are informed of potential health benefits, such as improved physical function and cognition. Verbal encouragement and group-based goal tracking are introduced to reinforce progress. Small rewards (e.g., certificates, recognition in group meetings) are given based on attendance and effort
	Enhance subjective norms	At baseline, participants are introduced to peer role models and encouraged to train alongside others in their nursing home. Staff highlight the social benefits and collective identity of participating in the program. Group norms are reinforced by praise and mutual encouragement
	Enhance social support	Sessions are facilitated by a consistent instructor to build trust. Nursing home staff are encouraged to support participants. Peer support is fostered through shared exercises and group discussion
	Enhance attitudes	Educational sessions are held at the start of the intervention, featuring short talks or videos on the benefits of exercise for aging and cognitive health. These are followed by Q&A and small-group reflections to reinforce positive attitudes
**Intender** (from preintenders to intenders)	Action planning	Supervisors work with participants to plan when and how they will attend twice-weekly group sessions. Participants receive a printed plan outlining the frequency, intensity, duration, and type of exercise based on the FITT-VP principle
	Coping planning	Instructors discuss common barriers to participation (e.g., fatigue, joint pain, scheduling) and guide participants through generating coping strategies. Group sharing and encouragement are integrated into each session
	Improve maintenance self-efficacy	Participants are reminded of their ability to maintain training through positive reinforcement, feedback, and group support. Progress charts are displayed to visualize adherence
**Actor (action)**	Enhance recovery self-efficacy	For participants who miss sessions or experience difficulty, instructors provide reassurance and strategies for re-engagement. Group discussion and facilitator check-ins help normalize setbacks
	Reduce risk perception	Facilitators proactively address safety concerns and physical discomfort. Stretching routines, monitoring of vital signs, and individualized modifications are provided to reduce fear of injury

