#### Analysis of the primary outcome and secondary outcomes

The primary outcome (MoCA-B score) will be analyzed using linear mixed-effects models (LMM) within a Difference-in-Differences (DID) framework. All available time points (baseline, week 6, week 12, and week 24) will be included in the primary LMM analysis. Fixed effects will include group, time, and the group-by-time interaction, along with relevant baseline covariates (e.g., age and sex). The DID estimate corresponds to the group-by-time interaction term at week 12, representing the between-group difference in change from baseline to week 12 (the primary endpoint). Short-term (baseline to week 6), long-term (baseline to week 24), and durability effects (week 12 to week 24) will also be explored using the same framework. For secondary outcomes, continuous variables will be analyzed using similar linear mixed-effects models. Binary outcomes will be analyzed using generalized estimating equations (GEE) with a binomial family and logit link. Marginal predicted probabilities will be used to derive risk differences between groups. All analyses will be performed in the intention-to-treat (ITT) population.

Missing outcome data will be handled under the missing-at-random assumption using LMM models, which inherently accommodate incomplete repeated measurements. In addition, a sensitivity analysis will be conducted using multiple imputation with chained equations to assess the robustness of the primary results. Exploratory analyses for all outcomes will also be performed using per-protocol analyses to evaluate efficacy among participants who complete the intervention as specified and provide both baseline and 12-week outcome data. Subgroup analyses will be conducted to explore potential heterogeneity of treatment effects. Two-sided *p*-values of less than 0.05 will be considered to indicate statistical significance.

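### The first dropout criterion is met by full attendance at a twice-weekly programme, so the dropout count carries no information about adherence

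*Protocol article*

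**What the plan says.** **Schedule.** Under Intervention group, the protocol article states: "Participants in the intervention group will receive a 12-week, group-based multicomponent exercise program". On frequency it states: "Each session will last 30 min and will be conducted twice per week". The action-planning row of Table 2 repeats this: "Supervisors work with participants to plan when and how they will attend twice-weekly group sessions". Nowhere does the article offer a third weekly session.

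**Dropout rule.** Under Process evaluation: "Participants will be classified as having dropped out if they meet any of the following criteria". The criteria are:

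1. "average training frequency of ≤ 2 times per week over 3 weeks";
2. "average frequency of ≤ 1 time per week for two consecutive weeks";
3. a week in which no session is completed.

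Absences of one to two weeks for medical or personal reasons are excused if the participant then returns to full participation. Those classed as dropouts are still encouraged to attend follow-up assessments.

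**Where the rule is used.** The same section bases adherence on two things, a count of dropouts and how often sessions were attended, and speaks of both groups. The Abstract lists intervention feasibility among the secondary outcomes.

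**Analysis sets.** Primary and secondary analyses are by intention to treat. A per-protocol analysis, described as exploratory, is to assess "efficacy among participants who complete the intervention as specified" who also have outcome data at baseline and week 12. That sentence does not refer to the dropout criteria.

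**The concern.** A dropout definition should separate people who stopped attending from people who kept coming. Here the first threshold equals the number of sessions on offer and the inequality includes equality, so the best possible attendance falls on the dropout side. Because any one criterion is enough, passing the other two does not help.

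At stake is the feasibility evaluation. The intervention is built around behavioural strategies to sustain attendance, and the trial sets out to assess feasibility alongside effectiveness. A dropout count that comes out the same whatever participants do cannot inform that aim. If the rule is quietly repaired once attendance has been seen, the reported count will depend on a choice made with the data in view, and different repairs give very different counts.

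**Working it through.** The article gives no figure that depends on the dropout rule, so there is none to reproduce. The sample size (126, or 63 per group) does reproduce with an exact two-sample t-test at effect size 0.54, two-sided α = 0.05 and 85% power (power 0.8525 at 63 per group), but this point does not rest on it.

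**Inputs**

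- Sessions per week: 2 (Intervention group; Table 2).
- Programme length: 12 weeks (Intervention group), so 2 × 12 = 24 sessions.
- Criteria 1 to 3, any one sufficient (Process evaluation).
- Intervention arm: 78 participants (Results).

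**Step 1: perfect attendance (2 in every week)**

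| Criterion | Calculation | Met? |
|---|---|---|
| 1: mean over 3 weeks ≤ 2 | (2 + 2 + 2)/3 = 2.0 | Yes |
| 2: mean over 2 weeks ≤ 1 | (2 + 2)/2 = 2.0 | No |
| 3: a week with 0 sessions | weekly minimum is 2 | No |

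Criterion 1 alone makes the full attender a dropout.

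**Step 2: any other attendance.** Weekly attendance can only be 0, 1 or 2, so a three-week total is at most 6 and its mean at most 6/3 = 2.0. Every three-week window therefore meets criterion 1. Listing all 3^12 = 531,441 possible 12-week patterns confirms this: none escapes.

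**Step 3: the exemption.** It excuses temporary absences. A full attender has no absence to excuse, and the full participation that must follow an absence itself meets criterion 1.

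**Step 4: the other criteria.** Criterion 1 needs three weeks of observation. Criteria 2 and 3 can be met after two weeks and one week, so they still matter for someone who leaves very early. For anyone observed for three weeks or more, they change nothing in the final classification.

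**Step 5: does the choice of repair matter?** This step shows only how sensitive the rule is; it does not recommend a threshold.

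- With a strict inequality in criterion 1 (< 2), perfect attendance passes. One missed session in 12 weeks gives (2 + 2 + 1)/3 = 1.67 < 2, a dropout unless exempted. Setting the exemption aside, 1 of the 531,441 patterns escapes all three criteria.
- With criterion 1 removed and criteria 2 and 3 kept, 377 patterns escape.

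These are counts of possible patterns, not probabilities. They show that two simple repairs define quite different groups of dropouts.

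**Step 6: the control arm.** Controls have no sessions. Taken across both groups, criterion 3 would class every control as a dropout in the first week.

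**The case against.** The strongest reply is that this is a slip in the process evaluation with little reach. Much of that stands.

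- The primary and secondary analyses are by intention to treat, and people labelled as dropouts are still followed up. The label does not remove outcome data or alter the MoCA-B estimate.
- A reader might infer that reported adherence would be 0%. The article does not support that. Attendance frequency is a separate adherence measure, and a full attender would still show two sessions a week.
- A reader might infer that the per-protocol analysis has no intervention participants. The article defines that set in its own terms and does not link it to the dropout rule. On a plain reading, someone who attended 24 of 24 sessions completed the intervention. Any numeric cut-off may sit in the statistical analysis plan, which is not shown. The empty set follows only if the dropout rule is borrowed for this purpose.
- A reader might also infer that the exploratory per-protocol analysis needs replacing by another method. That does not follow from an error in the dropout definition.

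The reply that the intended meaning is obvious does not stand. The article does not show whether the schedule, the inequality or the threshold is at fault, and step 5 shows that the choice changes who counts as a dropout. Nor can this be left to an unseen analysis plan: the article states the rule in full, and in a form that cannot work.

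**Conclusion.** The first dropout criterion contradicts the twice-weekly schedule. Applied as written, it classes every intervention participant observed for at least three weeks as a dropout, up to 78 of 78 and including anyone with complete attendance. The dropout count then says nothing about adherence, and neither would a retention figure built on it.

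The conclusion assumes that two sessions a week is the maximum on offer, as both statements of the schedule say, and that the criteria are read literally.

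The point should be fixed, but it does not threaten the main result. Session frequency and the intention-to-treat analyses are unaffected, and any effect on the exploratory per-protocol set depends on a link that the article does not make.

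**What to change.** Issue a dated correction, before database lock and without sight of outcomes, that does the following:

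- reconciles the dropout criteria with the session schedule so that full attendance cannot count as dropout, for example by expressing each criterion as a share of scheduled sessions, with the sponsor setting the cut-off;
- applies the session-based criteria to the intervention arm only;
- uses the corrected definition wherever dropout or per-protocol status depends on attendance, and says whether the per-protocol set does depend on it.

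Recruitment was expected to end by March 2025, so attendance data may already exist. If they have been looked at, the correction should say so.

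The cost is about one sentence in the protocol and the matching line in the statistical analysis plan. No new data are needed, because adherence records are already planned.

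### Even with its first criterion set aside, the dropout rule follows the pattern and recorded reason of missed sessions, so a 22/24 attender can be a dropout while a 20/24 attender is exempt

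*Protocol article*

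**What the plan says.** The Intervention group section fixes the length and frequency: "Participants in the intervention group will receive a 12-week, group-based multicomponent exercise program", and "Each session will last 30 min and will be conducted twice per week". The total of 24 sessions is not stated but follows from these.

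The Process evaluation section names two adherence measures, the dropout count and session frequency. It defines the first as follows: "Participants will be classified as having dropped out if they meet any of the following criteria". The criteria are:

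1. "average training frequency of ≤ 2 times per week over 3 weeks"
2. "average frequency of ≤ 1 time per week for two consecutive weeks"
3. "no sessions completed within a 1-week period"

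An exception follows directly: "Temporary absences of 1–2 weeks due to medical treatment or personal reasons will be exempt if participants resume full participation thereafter". Dropouts are still to be encouraged to attend follow-up assessments.

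Table 2 plans for missed sessions in the actor phase: "For participants who miss sessions or experience difficulty, instructors provide reassurance and strategies for re-engagement".

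**The concern.** A dropout count is normally read as the number of people who stopped. Here the second and third criteria act on windows of one or two weeks, and the exemption turns on whether the absence fills whole weeks, what reason is recorded and whether attendance then resumes in full. A participant who never stopped can be counted as a dropout, while one who attended fewer sessions is not.

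This matters because the count is one of only two stated adherence measures. Better adherence is a stated aim of the theory-based programme, and feasibility is a listed outcome. A reader of the results would take the count as discontinuation, although many of those counted might still be attending.

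**Working it through.** **Inputs.** Two sessions per week for 12 weeks (Intervention group section): 2 × 12 = 24 sessions. The criteria and the exemption come from Process evaluation. The documents give no attendance rate and no expected dropout count under this rule, so there is no plan figure to reproduce.

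**Criteria as session counts.**
- First: at most 2 × 3 = 6 sessions in 3 weeks. Full attendance gives exactly 6, so even a 24/24 attender meets it. It is set aside from here on.
- Second: at most 1 × 2 = 2 of the 4 sessions in two consecutive weeks.
- Third: 0 of 2 sessions in a week. An empty week next to a full one totals 2, so it also meets the second criterion.

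**Two participants side by side.**

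| Weekly attendance | Sessions | Second criterion | Third criterion | Exemption | Label |
|---|---|---|---|---|---|
| 2, 2, 1, 1, then 2 throughout | 22/24 = 91.7% | met (1 + 1 = 2) | not met | literally none: no week of absence | dropout |
| 2, 2, 0, 0, then 2 throughout, personal reason | 20/24 = 83.3% | met | met | applies | not a dropout |

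**How general this is.** There are C(24, 2) = 276 ways to miss two of 24 sessions.
- Both misses in the same week: 12.
- One miss in each of two adjacent weeks: 11 adjacent pairs × 2 × 2 = 44.
- Neither criterion met: 276 − 12 − 44 = 220 (80%).

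So 56 patterns (20%) meet the second or third criterion. If every whole-week absence has a qualifying reason, the exemption excuses 11 of the 12; an empty week 12 leaves no session to resume. That leaves 45.

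Of the 10,626 ways to attend 20/24, 2,016 meet neither criterion even without the exemption, for example single misses in weeks 1, 3, 5 and 7. The reversal therefore does not depend on the exemption. These are counts of arrangements, not probabilities.

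**Size under an assumption.** Let each session be attended independently with probability p. A week is full with probability p², has one session with probability 2p(1 − p), and is empty with probability (1 − p)². To be as generous as possible to the exemption, leave out everyone with any empty week and count only those with two adjacent one-session weeks.

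- P(no empty week) = [1 − (1 − p)²]^12.
- P(no empty week and no two adjacent one-session weeks) = a₁₂ + b₁₂, where a₁ = p², b₁ = 2p(1 − p), aₖ₊₁ = (aₖ + bₖ)p² and bₖ₊₁ = aₖ · 2p(1 − p).
- The share labelled is the difference.

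| p | P(no empty week) | a₁₂ + b₁₂ | Dropout with no empty week |
|---|---|---|---|
| 0.95 | 0.9704 | 0.8844 | 0.0860 (8.6%) |
| 0.90 | 0.8864 | 0.6412 | 0.2452 (24.5%) |
| 0.85 | 0.7610 | 0.3973 | 0.3637 (36.4%) |

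**The case against.** The strongest reply is that, as written, the rule labels both participants in the example as dropouts, because the first criterion catches everyone. The contrast appears only once that criterion is set aside. This is true, and it is why the point is secondary. But the reversal comes from the second criterion and the wording of the exemption, so correcting the first criterion alone would leave it in place.

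Some stronger readings are tempting, and the documents do not support them:

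- A reader might infer that the third criterion and the exemption contradict each other. They do not. The exemption is an explicit, conditional exception, and an empty week followed by resumption is just the case it covers. What remains is that personal reasons are not delimited and that resumption is known only later.
- A reader might infer that every 22/24 attender is a dropout. Most patterns (220 of 276) meet neither remaining criterion.
- A reader might quote the share meeting the second or third criterion before any exemption, about 12%, 36% and 60% at the same attendance levels. Those figures ignore the exemption.
- A reader might infer that the label blocks the re-engagement in Table 2. Nothing says that a person labelled a dropout is barred from sessions or support.
- A reader might infer damage to the efficacy results. The primary analysis is by intention to treat, and the per-protocol definition does not cite this rule.

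It is also fair to say that session frequency is already an adherence measure, so exercise received is not lost. That limits the harm and makes the correction easy, but it does not make the dropout count interpretable.

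**Conclusion.** The point holds in a limited form. With the first criterion set aside, the remaining rule can classify a participant with 92% attendance as a dropout, with no exemption on a literal reading, and exempt one with 83%. Which label results depends on how the misses fall and what reason is recorded.

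About 9%, 25% and 36% of participants would be labelled without having had an empty week at 95%, 90% and 85% attendance. These figures rest on independent misses, calendar weeks, assumed attendance levels and a literal reading of absence. Misses clustered by illness would give different figures. If single misses in adjacent weeks were treated as a temporary absence, the exemption could reach some of these participants, but the text does not say so.

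The consequence is a potentially misleading dropout count in the adherence and feasibility report. It is worth correcting because the correction is cheap, but it does not threaten the primary result.

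**What to change.** Reconcile the criteria and the exemption in the same edit that corrects the first criterion:

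- Report sessions attended out of 24, as a count and a proportion, as the adherence measure. Temporary absences then simply show as missed sessions.
- For reporting, count as discontinued only a participant who stops and attends no further session up to week 12, with the date of the last session and the reason.
- The short-window criteria and the reason-based exemption are then no longer needed for this count.

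The cost is wording in the protocol and analysis plan; session frequency and reasons for drop-off are already to be collected. The downside is that the count will differ from the one defined in protocol version 1.0, so that definition should be stated once alongside the new one.
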